### Assessment of Cognitive Performance, Cognitive-ISA and Metacognition

Each patient’s cognitive performance is evaluated at baseline measurement. To identify patients with mild cognitive impairment (MCI), MCI-Level II-Assessment is applied. To the best of our knowledge, no established neuropsychological test battery exists to perform level II testing. Therefore, we have compiled a test battery ourselves, while also taking into account the guidelines of diagnostic criteria for MCI in PD (Litvan et al., 2012). To differentiate between single- and multiple domains of PD-MCI, for research purposes it has been strongly recommended to use two different neuropsychological tests for each cognitive domain. Table 1 specifies the neuropsychological tests used for this purpose.

**TABLE 1 T1:** Overview of the applied neuropsychological test battery.

Domain	Test I	Test II
Attention/Working memory	TAP: Sustained attention	WMS-R: Digit span forward/backwards
Executive Functioning	RWT: Alternating semantic verbal fluency	Trail Making Test A + B
Language	WAIS-IV: Similarities	WAIS-IV: Vocabulary
Memory	VLMT	ECFT-MI: Recognition Trial
Visuospatial Ability	WMS-R: Spatial Span forward/backward	ECFT-MI: Matching Trial

*ECFT-MI: Extended Complex Figure Test – Motor Independent Version (Fastenau, 1996); RWT: Regensburg verbal fluency test (Aschenbrenner et al., 2001); TAP: test battery for attention (Zimmermann and Fimm, 2002); VLMT: Verbal learning and memory test (Helmstadter et al., 2001); WAIS-IV: Wechsler Adult Intelligence Scale – Fourth Edition (Wechsler, 2008); WMS-R: Wechsler Memory Scale-Revised (Härting et al., 2000).*

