For time-economic reasons and to minimize patient strain, full MCI-Level II-Assessment cannot be performed during post- and follow-up measurement. To investigate the effects of mindfulness on cognitive performance regardless, one test for each domain is applied at these time points. For this purpose, tests listed in the column “Test I” are used. Each patient also completes the Montreal Cognitive Assessment [MoCA (Nasreddine et al., 2005)]. As mentioned before, some neuropsychological tests offer parallel versions. To minimize training effects caused by performing the same test more than once, the applied test version of the Regensburg verbal fluency test, the Verbal learning and memory test and the MoCA is chosen randomly for each patient. It is possible that the same test version is assigned to a patient more than once. In addition, neuropsychological data is used to evaluate two kinds of cognitive awareness. For one, self-awareness for performance level in daily life and secondly, metacognition for cognitive performance in neuropsychological tests.

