#### Impaired Self-Awareness of Cognition

To investigate impaired self-awareness of cognition (ISAc), subjective cognitive impairment in everyday life is compared with the more objective performance in neuropsychological tests. Subjective cognitive impairment in general is assessed by using the Cognitive Failures Questionnaire [CFQ (Broadbent et al., 1982)]. Additionally, for impairment of executive functions the Dysexecutive Questionnaire [DEX (Wilson et al., 1998)] is applied. Higher scores reflect higher subjective impairment in both questionnaires. For further statistical analysis, questionnaire and neuropsychological test raw data is transformed into standardized z-scores to allow better comparison. A delta score is calculated by subtracting subjective scores from objective scores. Beforehand, depending on the analytical objective, the transformed values of all neuropsychological tests are either summed up for reflecting general cognitive performance, or only verbal fluency performance is taken into account to reflect executive cognitive performance. Impaired self-awareness of cognition occurs if objective neuropsychological test performance appears to be worse than subjective impairment in everyday life. This is reflected by a positive delta score. A similar method has been used before to study anosognosia of memory deficits in Alzheimer’s Disease (Vannini et al., 2017).

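### General ISAc subtracts one CFQ z-score from an un-rescaled sum of test z-scores, so the score mostly reflects test performance and its sensitivity to changed self-report is heavily reduced

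*Protocol article*

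**What the plan says.** The construction is given in the Methods subsection Impaired Self-Awareness of Cognition.

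- Scaling: "questionnaire and neuropsychological test raw data is transformed into standardized z-scores to allow better comparison".
- Objective side, general version: "the transformed values of all neuropsychological tests are either summed up for reflecting general cognitive performance".
- Objective side, executive version: "or only verbal fluency performance is taken into account to reflect executive cognitive performance".
- Subjective side, general version: "Subjective cognitive impairment in general is assessed by using the Cognitive Failures Questionnaire". The Dysexecutive Questionnaire is added for executive functions.
- Contrast: "A delta score is calculated by subtracting subjective scores from objective scores". A positive result is read as impaired awareness.

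The number of tests comes from Assessment of Cognitive Performance, Cognitive-ISA and Metacognition. At baseline Table 1 lists two tests in each of five domains. At post and follow-up "one test for each domain is applied at these time points", namely the Test I column.

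Outcome Measures makes ISAc a secondary outcome, analysed as change from baseline to post and to follow-up. It lists neuropsychological test performance as a secondary outcome in its own right.

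**The concern.** The z-transformation is there so that tests and questionnaires can be compared. Summing several z-scores undoes this: the sum has a variance of at least the number of tests when they are non-negatively correlated, while the CFQ keeps a variance of 1. The difference then follows the larger component.

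Three uses are affected:

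- **Change in awareness.** If patients come to report their everyday failures more accurately while their test scores stay the same, only the lightly weighted side moves. Conversely, the Introduction considers gains in attention and executive function possible. A gain of 0.2 SD on each of five tests moves the sum by 5 × 0.2 = 1.0, as much as a full SD on the CFQ, with self-report unchanged.
- **The label.** The sign of the difference decides who counts as having impaired awareness.
- **Neural correlates.** Planned Statistical Analyses relates cognitive self-awareness to imaging. Correlates of this score would largely be correlates of test performance.

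The problem remains if exactly the same five tests are used at every visit, so it is separate from the reduction of the battery after baseline.

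**Working it through.** The article gives no figure for the ISAc score, so there is none to reproduce.

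**Inputs from the article.** Each component is a z-score. The number of tests k is 5 (Test I column) or 10 (full Table 1). The subjective side is one questionnaire. The 83 per group in Planned Statistical Analyses is used only for the power illustration.

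**Assumptions not in the article.** Z-scores are formed in the trial sample (SD 1 each). Mean inter-test correlation r is 0 to 0.5. The test sum and the CFQ are uncorrelated (relaxed in step 3). For power: a 0.5 SD group effect on the CFQ with tests unchanged, retest correlations of 0.7 to 0.9, and two-sided alpha 0.05.

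**1. Variance share.** Let S be the sum and D = S − CFQ. Then Var(S) = k + k(k−1)r, Var(D) = Var(S) + 1, and the test share is Var(S)/(Var(S)+1).

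**2. Weight of a CFQ shift.** A shift of c is c/√(Var(S)+1) in SD units of D. With S rescaled to SD 1 it would be c/√2. The fraction kept is √(2/(Var(S)+1)).

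| k | r | Var(S) | Test share | Fraction of CFQ shift kept |
|---|---|---|---|---|
| 5 | 0 | 5 | 5/6 = 83% | 58% |
| 5 | 0.3 | 11 | 11/12 = 92% | 41% |
| 5 | 0.5 | 15 | 15/16 = 94% | 35% |
| 10 | 0 | 10 | 10/11 = 91% | 43% |
| 10 | 0.3 | 37 | 37/38 = 97% | 23% |
| 10 | 0.5 | 55 | 55/56 = 98% | 19% |

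**3. Correlated components.** With both sides coded as impairment, a sum-CFQ correlation of 0.1-0.3 and r = 0.2-0.4, the squared correlation of D with S is 0.89-0.93 (k = 5) or 0.96-0.98 (k = 10). With the CFQ it is at most about 0.05.

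**4. The sign rule.** For normal, uncorrelated components the chance that D and S have the same sign is 1 − arccos(ρ)/π, where ρ = √(Var(S)/(Var(S)+1)). With k = 5 and r = 0.3, ρ = 0.957 and the chance is 91%. With k = 10 it is 95%. On equal scales ρ = 0.707 and it is 75%.

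**5. Illustrative power (k = 5, r = 0.3, 83 per group).** Each component's variance is multiplied by (1 − retest²) to reflect baseline adjustment.
- Retest 0.7 for both, as written: variance 12 × 0.51 = 6.12, SD 2.47, d = 0.5/2.47 = 0.20, power about 26%.
- The same, rescaled: variance 2 × 0.51 = 1.02, SD 1.01, d = 0.50, power about 89%.
- Tests 0.9 and CFQ 0.7: as written, variance 11 × 0.19 + 0.51 = 2.60, power about 52%; rescaled, variance 0.19 + 0.51 = 0.70, power about 97%.

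**6. Averaging instead of summing.** Var(mean) = Var(S)/k². For k = 5 this is 0.20 at r = 0 and 0.60 at r = 0.5, so the test share is 0.20/1.20 = 17% to 0.60/1.60 = 38%. The imbalance then runs the other way.

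**The case against.** The strongest reply is that a condensed article need not state every scaling step, and a full protocol may re-standardise the composite. That remains possible. But the article does set out the sequence of transforming, summing and subtracting, and no rescaling appears in it. Taken as written, the rule works against the purpose given for the z-scores.

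Second, the inputs are assumed. This is true of the correlations, the retest values and the 0.5 SD effect, and normative z-scores would not have an SD of exactly 1 in this sample. The direction does not depend on the choice of r, however: at r = 0, the mildest case in the range, the variance ratio is still 5:1.

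Third, a reader might infer that general ISAc can hardly register a change in awareness. The figures do not support that: with five tests a third to more than a half of the standardised shift is kept, and the loss of power is smaller when the tests are very stable. A reader might also compute power from the cross-sectional SD, which gives 15% against 62%. Those figures ignore the baseline covariate in Planned Statistical Analyses and should not be used.

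Fourth, the scope is narrow. The CFQ and the tests are also recorded separately, so a reader of the results could see which side moved. Strengths of This Study concedes that the ISAc analyses are not validated. No comparison of general with executive ISAc is planned, so their different scales harm no stated analysis. The imaging is optional and limited to up to 30 patients. All of this limits the harm, but none of it justifies the weighting.

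**Conclusion.** The point holds for general ISAc as described in the article. The objective and subjective sides are on different scales, and the score is dominated by test performance to the extent shown in the table. The sign rule would mainly sort patients by test score, and a group difference could not be read as a difference in awareness rather than cognition. The percentages rest on sample-based z-scores and on the stated correlation ranges. The power figures are an illustration only, since the article makes no power claim for ISAc.

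The finding goes no further than one version of one secondary outcome. The primary ISAm score is built differently, and executive ISAc sets a single test z-score against a single questionnaire z-score, so neither has this problem. It is worth correcting before analysis, but does not threaten the trial's main conclusion.

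**What to change.** State the general ISAc score in this order:

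1. Convert each test and the CFQ to z-scores, using the baseline mean and SD at all three visits.
2. Sum or average the same tests at every visit. Of the Table 1 tests, only the five in the Test I column are available throughout. Say whether the MoCA counts.
3. Divide the composite by its own baseline SD, so that its SD is 1 at baseline, and keep that divisor at later visits.
4. Only then subtract the CFQ z-score.

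In the uncorrelated case this gives a test share of 50% at baseline. Replacing the sum by a mean without step 3 is not sufficient, as step 6 of the working shows. Reporting the composite and the CFQ beside the difference would show which side moved.

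The cost is a short addition to the analysis plan and one rescaling step in the code. No new data, visits or patients are needed.

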#### Metacognition

In addition to comparing subjective cognitive performance in daily life, we also plan to compare the patients’ objective cognitive performance (according to normative value) to their estimated performance in neuropsychological tests. Therefore, each patient is asked to rate his/her performance compared to a healthy person of the same age, right after completing a neuropsychological test. On a 5-point Likert scale, the patient rates whether his/her performance is equal to the performance of the upper 20, 40, 60 or lower 20 or 40 percent of people the same age. By doing so, the patients are required to observe themselves from a metacognitive perspective. If the patients rate their own performance better than their objective test performance, the ability of metacognitive observation might be impaired.

### Questionnaires

To evaluate the effects of IPSUM on emotional well-being as well as other non-motor symptoms of PD, all patients are asked to complete several questionnaires. All questionnaires are filled out at all three measurement points. PD related symptoms of interest are depression [BDI-2], Apathy [Apathy Evaluation Scale – AES (Marin et al., 1991)], Impulsivity [Questionnaire for Impulsive-Compulsive Disorders in PD – QUIP (Probst et al., 2014)] and Sleeping Problems [Parkinson’s Diseases Sleep Scale-2 – PDSS-2 (Trenkwalder et al., 2011)]. Furthermore, to study changes of emotional well-being, experienced stress [Perceived Stress Questionnaire-20 – PSQ-20 (Fliege et al., 2005)], state and trait anxiety [State-Trait Anxiety Inventory – STAI (Spielberger, 2010)] and quality of life [Parkinson’s Disease Quality of Life – PDQ-39 (Berger et al., 1999)] are assessed. Data about subjective cognitive impairment in general [CFQ] and specifically for executive function [DEX] is needed to evaluate ISAc, as described above. Since this study intends to evaluate the effects of a mindfulness based intervention, trait mindfulness [German Version of the Five Facet Mindfulness Questionnaire – FFMQ-D (Marin et al., 1991; Michalak et al., 2016)] is also assessed.

### Imaging

Eligible patients are asked to undergo an optional MRI scan during baseline and post measurement to study potential neurobiological changes induced by the intervention. Additionally, the neurobiology of ISAm and ISAc can further be studied. The MRI protocol comprises a T1-weighted structural scan for morphometric analysis, a blood oxygen level-dependent (BOLD) resting state time series to analyze functional connectivity, as well as a diffusion-weighted sequence for tractography. Scans will be acquired on a 3T Siemens Trio MRI scanner. Currently up to 30 patients (15 per group) are planned to participate in the imaging measurement of this study.

### Semi-Structured Interview

Up to this date, the applied quantitative measurement of ISAm has not been used for longitudinal studies. Therefore, it is uncertain if the instrument is sensitive to changes over time. Because of that, every patient who successfully completed the intervention protocol can take part in a semi-structured interview focusing on the possible changes they noticed over the last weeks (Supplementary Table S1). This also includes possible side effects caused by the intervention. The interview takes place during post- and follow-up measurement. By collecting qualitative data, we hope to get a more detailed insight into changes induced by mindfulness, especially in regards of self-awareness, and their relevance for the patient’s everyday life. Additionally, feedback regarding the intervention itself can be collected to further improve the training protocol in the future.

### Intervention Protocol

IPSUM is an 8 weeks long, group-based intervention which seeks to improve mindfulness and self-awareness of motor symptoms in patients with PD. In this study, all training sessions are held by a psychologist (main author [name]). The concept is designed for groups of 4–8 patients and consists of 8 weekly sessions of approximately 2 h of duration. The main topic of a session differs from week to week. Table 2 gives an overview of all weekly topics.

**TABLE 2 T2:** Session Overview.

Week	Topic	Main goal
1	Introduction to the concept of mindfulness	Understanding the general concept in theory and by practice
2	The power of breathing	Understanding that we can only control our behavior (e.g., by experiencing the importance of breathing)
3	Thoughts and appraisals	Introduction to the concept of defusion from one’s own thoughts and appraisals and the importance of observing them
4	How to deal with emotions	Learning about the purpose of pleasant and unpleasant emotions and ways of self-care
5	Stabilization of mindful practice	Repetition of previously gained knowledge as well as solving current problems with daily practice
6	Mindfulness and stress resilience	Learning about the use of mindfulness techniques in regards of stress reduction
7	Moving meditation	Performing the complete sequence of sitting yoga composed of movements learned during the training
8	Closing session: A new beginning	Evaluation of the whole training participation and to find solutions for persisting problems of mindful practice to facilitate independent practice after the intervention has ended

While each session’s general topic is different, various recurring elements can be highlighted. For once, each week contains of a short theoretical input which fits the weekly topic. To account for possible impairment of attention, concentration or general cognition, this aspect will not exceed a duration of 15 min. A practical exercise which builds on the theoretical input is performed.

Secondly, patients practice guided mindfulness meditation in a group setting. To prevent patients from falling asleep or cancel meditation practice, various elements of gentle movement and muscle tensing and releasing are included. Additionally, some basic yoga movements are taught. To account for the impaired mobility of patients with PD, sitting yoga on a chair is practiced. At the end of the intervention each patient will have learned a simple yoga sequence which they can also perform at home. As the ability to describe one’s own experience (instead of judging it) is central to the concept of mindfulness, this part is extended by a small sensory exercise. Here, patients are handed a different object each week (e.g., wool or a heat pad) and are asked to describe it as detailed as possible using all five senses. As noted in a previous study of a mindfulness intervention with PD patients, patients find it helpful to focus on external stimuli instead of internal sensations alone (Birtwell et al., 2017).

Previous research also has shown that the time invested for mindfulness practice is of high importance. Therefore, each week patients are asked to practice body scan and mindfulness meditation at home using an audio CD with guided instructions. Since all participants are meditation beginners and also might have attentional deficits, practice time is raised each week, up to 30 min a day. To support the implementation of mindfulness into the patients’ everyday life, they are also asked to perform an informal mindfulness exercise which changes weekly, e.g., mindful walking or mindful eating. If possible, the time used for mindful practice should be noted in a journal for future analyses.

Starting in week two, each session will begin with a reflection of the week before. Here, the patients get the opportunity to talk about their experiences with the previous week’s homework and possible difficulties they might have encountered. The group setting is expected to be quite helpful for sharing common experience among the patients and getting support to overcome possible problems that may arise during daily practice. At the end of each session, each patient receives a brief written summary containing all relevant information of the theoretical input to allow reviewing specific details of the newly learned information as needed and to support independent practice at home. To continue mindfulness training at home, patients are asked to further practice 30 min of daily mindfulness meditation in addition to improving their informal mindful practice. To ensure compliance, patients are asked to note down all performed mindfulness exercises in tables contained in their written summary for another 8 weeks.

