### Study Design

To evaluate the effectiveness of IPSUM on ISAm an adaptive pre-post-design is applied. First, eligible patients are randomized into an intervention group and a waitlist control group. After approximately eight to twelve patients have been successfully recruited, they are randomized by a computer program. Patients of the intervention group are measured at three points in time: before, directly after and 8 weeks after the intervention has ended. As stated before, the intervention takes place between the first two measurements and continues for 8 weeks. Patients of the control group are measured at the same time intervals, but do not take part in the intervention and are therefore treated as usual. For ethical reasons those patients can participate in the intervention after the study has ended. Figure 1 gives an overview of the course of the study.

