## Discussion

The phenomenon of anosognosia has been described for various neurological diseases. Recently a less extreme version, the phenomenon of impaired self-awareness, has been observed in non-demented, non-depressed patients with PD. While it has been mostly reported for motor symptoms, it might also occur for cognitive or other non-motor symptoms. Based on scientific research, mindfulness training is suggested as a possible therapy concept. However, existing mindfulness interventions often do not consider the specific needs of patients with PD, e.g., decreased mobility or attention deficits. Therefore, we developed IPSUM, a new mindfulness-based intervention. IPSUM does not only consider the special needs of PD patients, but also has a larger focus on the aspect of self-awareness compared to other mindfulness interventions. While its feasibility and effectiveness in regards to impaired self-awareness of motor symptoms are the primary objectives of this study, we also want to evaluate changes of cognitive performance and self-awareness, as well as other non-motor symptoms and emotional well-being. As some patients undergo an fMRI scan, we hope to get better insight into the neurobiological changes caused by mindfulness training in PD patients with impaired self-awareness. Additionally, to evaluate the feasibility of IPSUM and to investigate the impact of mindfulness on the patient’s daily life, a semi-structured interview is conducted.

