## Conclusion

In conclusion, we expect this study to prove the feasibility and preliminary effectiveness of IPSUM, a newly developed mindfulness-based group intervention for the specific needs of PD patients, by increasing self-awareness of motor and cognitive symptoms and also increasing the patient’s quality of life on many levels.

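### Feasibility is a primary objective but is to be judged from interviews offered only to completers, and home practice before the primary endpoint need be recorded only where possible

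*Protocol article*

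**What the plan says.** **Feasibility.** The Discussion states that "its feasibility and effectiveness in regards to impaired self-awareness of motor symptoms are the primary objectives of this study", and the Conclusion adds that "we expect this study to prove the feasibility and preliminary effectiveness of IPSUM". Outcome Measures lists motor self-awareness as primary and a long set of secondary outcomes, none of which is a feasibility outcome. The method given for feasibility is in the Discussion: "Additionally, to evaluate the feasibility of IPSUM and to investigate the impact of mindfulness on the patient’s daily life, a semi-structured interview is conducted". The section on the interview says that "every patient who successfully completed the intervention protocol can take part in a semi-structured interview", and Study Design has the same restriction. The abstract instead says that each patient will be interviewed.

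**Practice records.** Intervention Protocol says that earlier research shows the time spent practising to matter greatly. It assigns daily home practice that rises weekly to 30 minutes. For this period it asks: "If possible, the time used for mindful practice should be noted in a journal for future analyses". For the time after the course, with the stated aim of ensuring compliance, "patients are asked to note down all performed mindfulness exercises in tables contained in their written summary for another 8 weeks".

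**Timing.** The primary analysis concerns the change from baseline to the post visit. Study Design describes the three visits as "before, directly after and 8 weeks after the intervention has ended".

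**The concern.** A feasibility study needs above all to hear from patients who stopped coming or did not practise. An interview reserved for completers cannot supply that, and its findings will lean towards those for whom the programme worked as planned.

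The practice record has a similar weakness. A diary kept only where possible is more likely to be kept by those who practise, so the record for weeks 1–8 would tend to be selective in the direction of good adherence. These are the weeks that lead to the primary endpoint. If motor self-awareness does not change, the investigators will want to know whether the programme failed or was not practised. An incomplete diary answers that poorly, and minutes not noted at the time cannot be reliably recovered later.

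**Working it through.** **1. How much of the programme is home practice?** The article gives no total and no split, so there is no stated figure to reproduce.

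Inputs from Intervention Protocol: 8 sessions of about 2 h, and daily home practice raised weekly to at most 30 min. The starting duration and the shape of the increase are not given.

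Assumptions: a linear increase from a start of *s* min/day to 30 min/day, counted over 8 full weeks (56 days) or over the 7 weeks between sessions (49 days).

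- Sessions: 8 × 120 = 960 min = 16 h.
- Home minutes = days × (s + 30)/2.
- Home share = home / (home + 960).

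| Start s (min/day) | Mean (min/day) | Home h, 49 days | Share | Home h, 56 days | Share |
|---|---|---|---|---|---|
| 1 | 15.5 | 12.7 | 44.2% | 14.5 | 47.5% |
| 5 | 17.5 | 14.3 | 47.2% | 16.3 | 50.5% |
| 10 | 20.0 | 16.3 | 50.5% | 18.7 | 53.8% |
| 15 | 22.5 | 18.4 | 53.5% | 21.0 | 56.8% |
| 30 (ceiling) | 30.0 | 24.5 | 60.5% | 28.0 | 63.6% |

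Home practice equals session time at 960/49 = 19.6 or 960/56 = 17.1 min/day on average. On a linear increase this means a start of 2 × 19.6 − 30 = 9.2 or 2 × 17.1 − 30 = 4.3 min/day (using unrounded means). The share before the post visit is therefore about 44–64%. Informal exercises have no stated duration and are not counted; they would raise it.

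**2. Recording, period by period.**

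| | Weeks 1–8 | Following 8 weeks |
|---|---|---|
| Endpoint that follows | Primary | Secondary |
| Home practice assigned | Rising to 30 min/day | 30 min/day: 56 × 30 = 1680 min = 28 h |
| Explicit recording rule | Journal, if possible | All exercises, in tables |

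The stricter request is stated for the period after the primary endpoint. The reference to another 8 weeks may mean that the same tables were already in use during the course. The text does not settle this, so the two statements need reconciling.

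**3. Who informs the feasibility objective?** The method named is the interview. Those eligible, according to the interview section and Study Design, are completers. The abstract says each patient. These too need reconciling. Planned Statistical Analyses names completed sessions as a possible moderator and says that the reason for and timing of dropout are recorded, but it links neither to feasibility.

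**The case against.** A reader could fairly reply as follows.

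- **Feasibility does not rest on the journal.** This is right. The journal is kept for later analyses and the interview is the named method. It might be inferred that feasibility would be demonstrated from diaries of willing recorders, but no section says so. The weakness lies in the completers-only interview.
- **Other information exists.** Session counts, dropout reasons and the mindfulness questionnaire, completed by all patients at all three visits, give a partial check on a null result. This stands, so the loss is a limit on interpretation and not a complete block. None of them measures practice time.
- **This is a condensed article.** Diary forms and feasibility thresholds may be in the full protocol. For the same reason one cannot conclude that waitlist patients are never asked about practice; the article is merely silent. But the completers-only interview and the optional journal are choices that the article states.
- **The follow-up visit is correctly labelled.** It is tempting to read the assigned practice up to follow-up as contradicting the description of that visit. The article defines the intervention as the 8-week course and openly describes independent practice afterwards, so the label is consistent. What remains is a caution that the change to follow-up does not show persistence once practice stops.

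**Conclusion.** The concern holds in limited form, as a cheap improvement and not a threat to the main result. A declared primary objective has no listed outcome, and its named method excludes the patients most informative about it. Adherence before the primary endpoint, for a component that is roughly 44–64% of assigned formal time, has only an optional record as its explicit rule.

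The range rests on the assumed linear increase and on counting 7 or 8 weeks. A reader might state flatly that home practice is more than half of the dose. That is true at the ceiling (60–64%) and on many of the increases tried, but the article does not fix it for the period before the post visit.

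The randomised primary comparison is not biased by any of this, since the article prefers analysis by intention to treat and practice time does not enter the primary contrast. The size of any overstatement of adherence cannot be estimated, because the documents give neither journal return rates nor practice minutes.

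**What to change.** 1. Use the existing practice table from week 1. Collect it at sessions 2–8, with zero minutes entered explicitly so that none can be told from missing. Collect it on paper or individually, not aloud in the group. Any days after session 8 can be collected at the post visit.
2. Judge feasibility on attendance, retention and recorded practice in all patients randomised to IPSUM, and treat the interview as supporting evidence.
3. Reconcile the two statements on recording in Intervention Protocol, and the abstract with the Methods on who is interviewed.
4. Optionally, describe the baseline-to-follow-up change as the effect of the course plus 8 further weeks of assigned home practice.

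The assigned practice itself does not change. The cost is a few minutes per session and a slight extra burden on patients. Practice minutes remain self-reported and open to social desirability, which private collection reduces but does not remove.
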